### Retention

Participants will receive a weekly email from the research team, which aims to promote adherence to the intervention and retention in the study. Follow-up data will be collected from all available participants irrespective of their compliance to the intervention.

### Criteria to indicate that a future effectiveness trial is feasible

Drawing on suggested criteria [23, 41] decisions on whether to proceed to an effectiveness trial is warranted will be determined on the basis of (1) meeting stated recruitment (57 participants within 1 month) and retention (retaining 80% of participants from pre-intervention to post-intervention follow-up) targets; (2) participants expressing that the conduct of the intervention was acceptable, that the components contained with the intervention were useful, and that any implementation barriers experienced by participants can be overcome; (3) that at least 50% of the sample recorded an average of at least 8 (half of the possible 16 in an eight hour day) opportunities to move at the end of the intervention; and (4) within and between estimates of variation in health indicators of interest can be observed, to inform the appropriate sample size calculation for an effectiveness trial.

### Data management

Due to the low risk nature of the trial, a data monitoring committee was not deemed necessary. All self-reported data will be directly input via online surveys to the web-based data capture system REDCap hosted at the University of Otago. All objective data collected at face-to-face sessions (e.g., weight, height, blood pressure) will be collected on hardcopy and then input to REDCap. Data entry will be double checked. The REDCap database that contains the study data represents each participant by an ID number and will be password protected. Accelerometer data will be saved in files identified by an ID number and will be saved on a password protected server. Only the research team will have access to the dataset. The de-identified information collected as part of this research will be retained for at least 10 years in secure storage.

### Adverse events

The intervention is not expected to result in any serious harm or adverse event. Participants will be asked to report any physical activity-related serious adverse events to the principal investigator. In the unlikely event that an injury is sustained, then participants will be covered by New Zealand’s Accident Compensation Corporation scheme.

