At the beginning of each week of the intervention period, participants will receive an email reminding them to set weekly action and barrier-coping plans. Participants will be asked to respond to the weekly email by sending back a copy of their action and barrier-coping plan to the research team (to indicate they have completed their plan). They will also be asked to email back a copy of the chart which detailed the number of opportunities to move performed on each day of the previous week.

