#### Change in physical activity behaviour

The number of opportunities to move that have been taken and 24 h patterns of physical activity will be identified using output from two accelerometers worn for 24 h a day for seven days at each assessment period. The ActiGraph Gt3x+ accelerometer is worn on an elasticated strap around the waist so that the accelerometer sits over the right hip (which provides accurate information about intensity of activity). The ActiGraph will be initialised to record activity at a sampling rate of 30 hz without the low-frequency extension. The ActivPAL3 is attached to the midpoint of the front of the right thigh with an adhesive dressing (which provides accurate information about posture). Prior to attachment, the ActivPAL will be inserted into nitrile two finger cots secured using a piece of adhesive to ensure it is water proof.

During each 7-day wear period, participants will complete a wear time diary, in which they will record times when either accelerometer was removed for more than 10 min (to identify non-wear time, e.g., for swimming or playing contact sport), times of day spent at work, and the time they attempted to fall asleep at night and got up in the morning.

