*Musculoskeletal health* will be assessed using the Standardised Nordic Questionnaire [33]. This measures musculoskeletal problems in nine body areas (neck, shoulder, upper back, elbow, wrist, lower back, hip, knee, and ankle). Participants respond either yes or no to whether they have had experienced any trouble in each body area and, if so, how much pain was experienced on a scale of 1 to 10. A lower score signifies better musculoskeletal health. Similar to Dunstan et al. [34], the wording will be modified to refer to the last 7 days and last 3 months (instead of 12 months).

*Psychological well-being* will be assessed using the Positive and Negative Affect Schedule — short form (PANAS) [35]. This scale assesses two sub-scales: negative affect and positive affect. Participants report on a 5-point Likert-type from 1 (never) to 5 (always) the extent to which they generally feel each of the 10 items. Lower scores on the negative affect subscale and higher scores on the positive affect subscale represent better psychological well-being.

*Work engagement* will be assessed using the Utrecht Work Engagement Scale 9 [36] which comprises three sub-scales: vigour, dedication, and absorption. Participants record on a 7-point Likert scale (0 [never] to 6 [always, every day]) how frequently they have had a particular feeling described in each item. Higher scores represent greater work engagement.

*Occupational fatigue* will be assessed using the 11-item Need for Recovery Scale [37]. The scale assesses the extent to which work tasks induce a need to recuperate from work induced effort. Participants report with a yes or no to each of 11 items. The sum of the items scored as ‘no’, is multiplied by 100 and divided by 11 (the total number of scale items) resulting in an overall score between 0 and 100. A higher score reflects a greater need for recovery and increased short-term work-related fatigue.

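### Adverse event collection is limited to events the participant considers both serious and activity-related, so minor injuries and procedure reactions are not recorded as adverse events

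*Protocol article*

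**What the plan says.** Under *Adverse events* the protocol article first gives an expectation: "The intervention is not expected to result in any serious harm or adverse event". It then gives the collection rule: "Participants will be asked to report any physical activity-related serious adverse events to the principal investigator". Injury is mentioned only in terms of compensation: "In the unlikely event that an injury is sustained, then participants will be covered by New Zealand’s Accident Compensation Corporation scheme". *Data management* adds: "Due to the low risk nature of the trial, a data monitoring committee was not deemed necessary".

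Three other sections gather information that bears on harm.

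- The musculoskeletal paragraph under *Measures* uses the Standardised Nordic Questionnaire. It asks about trouble in nine body areas and pain from 1 to 10, with recall of 7 days and 3 months. *Pilot study outcomes* schedules it at T1, T2, T3 and T4.
- *Feasibility: recruitment, retention, and acceptability* plans T3 interviews that include how participants found the accelerometers and blood collection. It also seeks reasons for dropping out where that is possible.
- *Retention* says follow-up data are sought from all available participants, whether or not they comply.

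The progression criteria cover recruitment and retention, acceptability ("participants expressing that the conduct of the intervention was acceptable, that the components contained with the intervention were useful", with a further clause on overcoming barriers), the number of opportunities to move, and estimates of variation. None refers to harm.

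**The concern.** An article may leave forms, definitions and reporting timelines to a fuller protocol. Here it does state which events are sought, and that choice excludes the harms most likely to occur. The coach's examples include stair walking, squats, calf raises and repeated chair rises, and the progression criteria count 16 possible opportunities in an eight-hour day. Plausible harms of such activity are minor strains, stumbles and flares of joint or back pain, which are seldom serious.

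Reactions to study procedures are not caused by physical activity, so they are outside the rule by definition. "The ActivPAL3 is attached to the midpoint of the front of the right thigh with an adhesive dressing", and it is worn round the clock for a week in each of four measurement waves. Fasting blood is also drawn.

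The study exists to decide whether a larger trial should follow and to refine the intervention. A statement that no adverse events were reported would read as evidence of tolerability. Under this rule it would carry no information about non-serious events.

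**Working it through.** The plan gives no figure for harms, so there is none to reproduce. The check sets each kind of event against each place where it could be picked up.

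| Event | Adverse event rule | Other source in the article |
|---|---|---|
| Serious, activity-related | Recorded if the participant reports it | Possibly the sources below |
| Non-serious strain, fall or pain from the breaks | Not recorded | Nordic questionnaire, as an outcome score; drop-out reasons, where possible |
| Skin reaction to the thigh device | Not recorded | T3 interview, as acceptability themes |
| Blood-draw reaction | Not recorded | T3 interview, as acceptability themes |

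**What the other sources yield.** The Nordic questionnaire is solicited from everyone. At T3 its 3-month recall spans the 12-week intervention, so it does register musculoskeletal symptoms. However, *Data analysis* treats it like the other outcomes: a mixed model reported as mean change with a 95% CI. In a mean change, less back pain in some participants can offset new knee pain in others. The score does not identify an event or its cause. The primary analyses keep only participants with data at T1, T2 and T3, so a person who is injured and provides no T3 data is left out of them. The interviews are coded for themes, so they yield no counts.

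**Size, under a labelled assumption.** Let p be the proportion with a non-serious injury or new pain. The documents give no value. With the planned 57 participants (*Sample size*):

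- p = 5%: 57 × 0.05 = 2.85, about 3 people
- p = 15%: 57 × 0.15 = 8.55, about 9 people
- Number recorded under the rule: 0 in both cases, because none is serious

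**Exposure, as a ceiling.** At 16 opportunities a day, an assumed five-day week and 12 weeks, 16 × 5 × 12 = 960 per person, or 57 × 960 = 54,720 in all. Part-time staff are eligible and the adherence criterion is 8 a day, so actual exposure will be lower. For example, 8 a day on 3 days a week gives 8 × 3 × 12 = 288 per person.

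**What a zero count could exclude.** With zero events in n people and complete ascertainment, the one-sided 95% upper limit is 1 − 0.05^(1/n). That is 5.1% for n = 57 and 6.2% for n = 47. These limits come from the sample size alone and are not evidence against the rule. They apply only to events that would have been recorded, so they cannot be applied to non-serious ones.

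**The case against.** The activity is one to two minutes of light to moderate movement. Participants are screened with the PAR-Q, people with physical impediments are excluded, and a coach demonstrates the movements. A light system is reasonable, and the absence of a monitoring committee is not at issue.

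A reader might go further and infer that ordinary injuries are never captured, or that the trial is bound to report almost no harm. The documents do not support this. The Nordic questionnaire asks every participant about the relevant body areas twice before and twice after the intervention starts. Device and blood-draw experience is explored at T3. The gap concerns what is recorded and counted as an adverse event.

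Nor must participants come forward wholly unprompted: the rule says they are asked to report, and the timing of asking may be in the full protocol. An injured participant is not visible only as a drop-out either, because drop-out reasons are sought and follow-up does not depend on compliance. Finally, tolerability is not wholly absent from the go decision, since pain could be raised under acceptability or implementation barriers, or show up in retention.

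These points narrow the concern without removing it. None of these sources produces a count of events or of people affected, and none changes the scope that the rule states.

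**Conclusion.** The point holds in limited form. As stated, the rule records only events that the participant considers serious and activity-related. Non-serious injuries or pain from the breaks, and reactions to the device or blood draw, are not recorded as adverse events. The adverse event count is therefore uninformative about non-serious tolerability, and no progression criterion mentions harm explicitly.

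The number of events missed cannot be estimated from the documents; the 5% to 15% range is an illustration only. The conclusion rests on reading the rule literally, with the participant deciding what meets its two conditions. If the full protocol has a wider rule, the article's sentence misdescribes it and should still be changed. The primary outcome and its analysis are unaffected. This is a cheap improvement.

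**What to change.** Replace the reporting sentence under *Adverse events* with a rule along these lines: all participants are asked a standard question at the existing T2, T3 and T4 contacts, and at the drop-out contact, about any injury, new or worse pain, or skin or blood-draw reaction, whatever its seriousness or presumed cause. The investigator classifies seriousness and relatedness. Report the number of events, and the number of participants affected with a 95% CI, for everyone who started the intervention. Provide this summary to the progression decision.

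The weekly return ("They will also be asked to email back a copy of the chart which detailed the number of opportunities to move performed on each day") looks like a convenient carrier but should not be the main route. The chart is itself a self-monitoring component of the intervention, so adding an injury item alters what is being tested. Someone who stops the breaks because of pain may also stop returning it.

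The cost is one question at contacts that already take place, a short classification step and one small table. The downside is that some unrelated aches will be recorded, with no comparator group to set them against. The T2 answers give a pre-intervention reading that helps with interpretation but does not replace a control.

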## Discussion

Prolonged bouts of sitting have been associated with increased incidence of diabetes, cardiovascular disease, some cancers, and overall mortality [2–4]. Those in office-based employment are particularly susceptible to both high rates of sitting and accumulating that sitting time in long uninterrupted bouts during work hours [5]. Laboratory studies have shown the benefits to health when periods of prolonged sitting are interrupted every 20–30 min with a short (2 min) bout of activity [10, 11]. The Move More @ Work study will provide the next level of evidence for the benefits of this protocol by examining its feasibility and potential effects in a real world setting.

Our Move More @ Work intervention is underpinned by key behaviour change constructs and techniques known to motivate behaviour change [18, 19] and address the key barriers and facilitators [13, 15–17] that influence the ability to take opportunities to move and reduce sedentary behaviour. By investigating work productivity and manager/work colleague opinions of the participant’s involvement in the intervention, we provide evidence of its ‘real world’ applicability. If the study meets the stated progression criteria this will provide evidence that an effectiveness trial is warranted [42] and that the intervention has the potential to successfully attenuate the health risks associated with prolonged sitting in an at-risk population.

## Data Availability

The datasets used and analysed during the current study are available from the corresponding author on reasonable request.
